### SAFER pregnancy study: outcomes

The primary outcome is biochemically validated cessation of smoking or alcohol use at (Fig. 1):week 34−38 of gestation (if pregnant at inclusion or became pregnant during participation); orthe end of the project period if <34 weeks pregnant at the time; orthe last validation after six group sessions in those who did not become pregnant during participation.

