### SAFER pregnancy study: setting and participants

The study will be conducted in Zoetermeer, Benthuizen (small village that affiliated its care with Zoetermeer) and Rotterdam, the Netherlands. Previous research indicated that the municipality of Zoetermeer (approximately 125,000 inhabitants and 1300 livebirths annually) had the highest perinatal mortality in the Netherlands^41^, and it has a relatively large deprived population with likely clustering of risk behaviours such as smoking and alcohol use. Within Rotterdam (approximately 640,000 inhabitants and 7900 livebirths annually), more than half of children grow up in a neighbourhood with low SES and one in five children grow up in poverty^42^.

Women are eligible if:pregnant or having a wish to become pregnant within 6 months;smoking at least one cigarette a day and/or drinking at least three units of alcohol a week.

Exclusion criteria are:less than 18 years of age;more than 20 weeks pregnant;insufficient mastery of the Dutch language;unwilling to undergo urinary, and/or breath testing (when reporting smoking), and/or blood testing (when reporting drinking alcohol).urinary cotinine level below 50 µg/L, carbon monoxide (CO) level <7 parts per million (ppm) (when reporting smoking) or PhosphatidylEthanol (PEth) test below 7 µg/L (when reporting drinking alcohol) at inclusion;use of hard drugs.

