### SAFER pregnancy study: data analysis plan

The proportion of women who quit smoking or alcohol use at the primary endpoint will be calculated as the number of women that have quit at this endpoint divided by the total number of women included in the study. Furthermore, we will use (backward) logistic regression analysis to explore independent predictors of effectiveness of the intervention. Descriptive statistics will be used for the secondary outcomes and results will be reported in narrative and tabular form. Open questions within the questionnaires will be evaluated qualitatively using thematic content analysis.

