### SAFER pregnancy study: sample size calculation

Because vulnerable populations, as our target population, are difficult to reach and recruit for participation in medical research^57,58^ and because we aim to develop an intervention fit for the target population, we decided at this stage to pragmatically perform an uncontrolled before−after study. The overall aim is to obtain an estimate of potential effectiveness of the SAFER pregnancy intervention, while assessing its feasibility and acceptability. As such, findings from this study are ideally placed to inform design of a potential larger randomised experiment. The primary outcome is the proportion of women attaining sustained cessation of alcohol use and/or smoking. Because little research on interventions for alcohol cessation during pregnancy exists and only a small number of women were referred to the focus group study due to alcohol consumption, we based our sample size calculation primarily on smoking cessation. In a recent randomised controlled trial assessing the effectiveness of incentives to promote smoking cessation during pregnancy, 22.5% of the women in the intervention group reached the primary endpoint of cessation, versus 8.6% in the control group^59^. Accordingly, we set our true proportion to 25% and our null hypothesis proportion to 9%. With a power of 90% and a one-sided alpha of 2.5%, our intervention group would have to contain 49 participants in order to assess effectiveness of the SAFER pregnancy intervention versus the counterfactual scenario. Considering an expected dropout of 25%, we aim to include 66 women, who smoke and/or consume alcohol, at baseline.

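### The primary outcome counts stopping smoking or alcohol across all women, but its only benchmark (9% against 25%) is a smoking-cessation rate

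*Protocol article*

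**What the plan says.** All references are to the protocol article.

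- **Entry** (setting and participants): "smoking at least one cigarette a day and/or drinking at least three units of alcohol a week". Smokers, drinkers and women who do both form one cohort.
- **Primary outcome** (outcomes): "The primary outcome is biochemically validated cessation of smoking or alcohol use at" the endpoint that applies to the woman's pregnancy status.
- **Analysis** (data analysis plan): "The proportion of women who quit smoking or alcohol use at the primary endpoint will be calculated" with the number who quit "divided by the total number of women included in the study". It is not split by behaviour, and no rule is given for a woman who both smokes and drinks.
- **Sample size**: the outcome is worded differently here: "The primary outcome is the proportion of women attaining sustained cessation of alcohol use and/or smoking". The abstract also uses and/or.
- **Benchmark** (sample size): "we set our true proportion to 25% and our null hypothesis proportion to 9" per cent. Both follow a trial of incentives for smoking cessation in pregnancy, with 22.5% and 8.6% in its two arms. The article discloses this: "we based our sample size calculation primarily on smoking cessation".
- **Target**: "we aim to include 66 women, who smoke and/or consume alcohol, at baseline".

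**The concern.** The study has no control group, so the 9% is the only thing the observed proportion can be set against. It describes how often women stop smoking without the intervention. The outcome describes how often women stop smoking or drinking, in a sample where some may smoke only, some drink only and some do both.

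For a dual user, the chance of stopping at least one behaviour cannot be lower than the chance of stopping smoking. If some of those who keep smoking would stop drinking anyway, her unaided success rate is above 9%. The article expects such women: its introduction says the two behaviours often occur together, and the incentive table has a column for stopping both. For a woman who only drinks, 9% has no stated relevance.

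At stake is the reading of the headline result. A proportion above 9% could partly reflect unaided alcohol cessation and say nothing about smoking. The same numerator also appears to define effectiveness in the exploratory regression and success in the cost per successful quitter.

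**Working it through.** **1. The plan's own figure.** Inputs from the sample size section: p0 = 0.09, p1 = 0.25, one-sided alpha 0.025, power 90%, dropout 25%.

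n = [1.960 × √(0.09 × 0.91) + 1.282 × √(0.25 × 0.75)]² / (0.25 − 0.09)² = (0.5609 + 0.5549)² / 0.0256 = 48.6, rounded up to 49. Then 49 / 0.75 = 65.3, rounded up to 66. Both figures reproduce. The arithmetic is sound, and the problem is what the 9% is compared with.

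**2. What exceeding 9% takes.** By exact binomial, the smallest count of 49 whose probability at a true 9% is at most 2.5% is 10 (probability 1.1%). Nine of 49 already has probability 2.9%, so it is not a 2.5% rule. If all 66 are the denominator, as the analysis section says, the count is 12 (1.4%).

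**3. The unaided rate for the outcome as written.** Let s, a and b be the shares of smoking-only, alcohol-only and dual users, and q the unaided alcohol quit rate. With no smoking effect, and the two behaviours independent in dual users:

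rate = 0.09s + q·a + b·[1 − 0.91(1 − q)]

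The documents give none of s, a, b or q. Everything below is an assumption shown as a range.

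**4. No alcohol-only women (a = 0).** The rate becomes 0.09 + 0.91·b·q.

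| Dual users (b) | Unaided alcohol cessation (q) | Unaided rate | P(≥10 of 49) | P(≥12 of 66) |
|---|---|---|---|---|
| 5% | 20% | 9.9% | 2.0% | 2.8% |
| 10% | 10% | 9.9% | 2.0% | 2.8% |
| 10% | 30% | 11.7% | 5.6% | 8.1% |
| 10% | 50% | 13.6% | 11.9% | 17.7% |
| 20% | 30% | 14.5% | 16.2% | 24.0% |
| 20% | 50% | 18.1% | 39.3% | 54.3% |

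**5. With alcohol-only women.** The direction now depends on q.

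- 60% smoking-only, 20% alcohol-only, 20% dual, q = 20%: 0.054 + 0.040 + 0.2 × 0.272 = 14.8%; P(≥10 of 49) = 18.2%.
- Same mix, q = 5%: 0.054 + 0.010 + 0.2 × 0.1355 = 9.1%; P(≥10 of 49) = 1.2%, almost unchanged.
- 70/20/10, q = 5%: 0.063 + 0.010 + 0.1 × 0.1355 = 8.7%, below 9%.

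**6. Number of smokers.** Nothing in the target of 66 guarantees 49 evaluable smokers. If 20% of 49 drank only, about 39 smokers would remain. At n = 39 the exact rule is 8 or more quitters, with power 79.4% at a true 25%. On the same exact basis n = 49 has 81.7%, so the loss is about 2 points. By normal approximation, which is how the plan reached 90%, n = 39 gives 84%.

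**The case against.** The strongest reply is that this is an uncontrolled feasibility study. The introduction names feasibility and acceptability as the primary aim, and the sample size section speaks of estimating potential effectiveness. The analysis section calculates a proportion and names no test against 9%. This stands: calling it a broken 2.5% error rate would treat a planning benchmark as a fixed confirmatory test. But the sample size section does set a null, an alpha and a power for this outcome, and says the 49 women serve to assess effectiveness against a counterfactual. A comparison with 9% is intended, even if its form is not stated.

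Second, few drinkers may enrol. All nine focus-group women took part because of smoking, and the sample size section says few were referred for alcohol. This also stands, and the bias may then be negligible, as the first rows of the table show. Nothing in the eligibility rules limits it, however.

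Third, the smoking basis is disclosed. Disclosure is to the plan's credit but does not make the outcome and the benchmark measure the same thing.

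Fourth, counting either behaviour may be intended, since the regular incentive is paid for stopping either. That is a legitimate outcome, but it would need its own counterfactual rate.

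A reader might also infer that the pooled percentage makes the data uninterpretable for each behaviour. The documents do not support that: smoking and alcohol are validated by separate tests, and Table 3 records the result of each assessment.

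**Conclusion.** The mismatch is real and follows from the text alone: a mixed sample, an either-behaviour outcome over all women, and a smoking-only benchmark. Read literally, a woman who stops drinking and keeps smoking is a success.

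Two stronger readings are tempting and fail. One is that the unaided rate must exceed 9% once any woman stops drinking. That holds for dual users, given that some who keep smoking would stop drinking unaided, but enough alcohol-only women with an unaided rate below 9% can cancel or reverse it (9.1% and 8.7% in step 5). The other is that loss of smokers cuts power from 90% to 79%. That sets an exact figure against an approximate one; like for like, the change is from 82% to 79%.

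The size of the bias cannot be fixed from the documents. With no smoking effect and no alcohol-only women, the chance of reaching 10 of 49 runs from about 2% to 39% over the assumed mixes, against 1.1% at a true 9%. These figures rest on assumed shares of dual users, assumed unaided alcohol cessation, and independence of the two behaviours. What is certain is that 9% is not a counterfactual rate the documents support for this outcome.

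**What to change.** - Make the comparison with 9% on biochemically validated smoking cessation among women verified as smokers at inclusion, and restate its power for the expected number of such women.
- Report alcohol cessation among women verified as drinkers at inclusion separately, with an exact confidence interval and no comparison with 9%.
- State one success rule for women who both smoke and drink. Abstinence from every substance verified at inclusion is one reasonable choice. If either behaviour is meant to count, say so and do not set that proportion against 9%.
- Use the same wording in the abstract, outcomes, data analysis plan and sample size sections.

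No new data are needed, because each behaviour already has its own test at inclusion and at the endpoint. The costs are that the smoking comparison may rest on fewer than 66 women, and that rewording the primary outcome of a registered and ethics-approved study needs a registered amendment. An all-substances rule would also lower the headline rate if some dual users stop only one behaviour.

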**Fig. 1 Fig1:**
[figure not shown]
Main study endpoints in relation to a participant’s pregnancy status*. *Primary study endpoints are marked with an asterisk. S1−S6 = sessions 1−6.

The secondary outcomes are listed in Table 3. We will collect costs at the individual level of running the programme including the web-based platform and the group sessions to estimate costs per successful quitter. Using estimates from existing meta-analyses on the primary adverse outcomes associated with the risk behaviour that has been avoided by the SAFER pregnancy approach, we will furthermore calculate crude estimates of potential cost-effectiveness.

**Table 3 Tab3:** Secondary study parameters/endpoints.

Data group	Data item	Data source
Barriers and facilitators of implementation (process measures)	How many sessions were attended by each participant	Study log
	How often participants logged in on the web-based platform	Smarter Pregnancy
	How many biochemical assessments were performed and the results of each assessment	Study log and lab results
	How many incentives were issued per person and in total	Study log
	How many local entrepreneurs were contacted and how many agreed to provide incentives	Study log
Perceived efficiency and appreciation of the web-based platform, the group sessions, and incentives	Experienced peer support and appreciation of the platform, the group sessions, and the incentives	Questionnaires
	Health behaviour before and during the study and after delivery	Questionnaires
	Reasons why lifestyle changes succeeded or failed	Questionnaires
	Evaluation of the group sessions	Questionnaires
Costs	The number of participants receiving incentives	Study log
	The amount of incentives received per participant	Study log
	The number of participants who achieve sustained cessation	Study log
Pregnancy outcomes	Date of delivery, singleton or multiple birth, birth weight, gestational age, gender, place of birth (e.g. hospital, home), type of delivery (e.g. caesarean section), Apgar score, admission to the Neonatal Intensive Care Unit (NICU), congenital abnormalities, mortality	Letter for the general practitioner if the participant consents, otherwise with a questionnaire
Identity changes	Identity factors associated with smoking status and/or drinking status	Questionnaire

### SAFER pregnancy study: data collection

Participants receive questionnaires through e-mail and fill them out online. They receive a voucher worth 15 euros if they filled out the questionnaire.

Questionnaire items are listed in Table 4. Participants receive a questionnaire at inclusion and 1 week before each group session. Women who are pregnant during the study period also receive a questionnaire at 34−38 weeks gestation and a final questionnaire 1 week postpartum. Women who do not become pregnant during the study period receive their final questionnaire after the sixth group session. In addition, a log on patient recruitment, collaboration with local entrepreneurs, and contact with healthcare providers and participants will be kept by the research team to explore barriers and facilitators for implementation of the intervention. In the log quantitative data will be noted, such as the number of potential participants referred and included and the amount of incentives provided (outcome measures are shown in Table 3). In addition, participants will fill out questionnaires about their experiences with the intervention and study itself during their participation and at the end of their participation. These data will give insight into acceptability and feasibility of the SAFER pregnancy intervention and therefore potential barriers and facilitators for proper implementation can be identified. These potential barriers and facilitators will be further qualitatively evaluated in a focus group study at the end of the SAFER pregnancy study, with the aim to evaluate the acceptability and feasibility of the intervention, in three separate focus groups with participants, leaders of the group sessions and involved healthcare providers.

**Table 4 Tab4:** Data collection with questionnaires.

Data group	Data item
Baseline characteristics	Age
	Parity
	Ethnicity
	Household income and financial problems
	Educational level
	Marital status and relational problems
	Due date
	Lifestyle behaviour (smoking, alcohol use, diet, activity, drugs)
	Statements concerning lifestyle changes according to the Attitude—Social influence—Self-efficacy (ASE)-model
	Statements concerning identity
Level of addiction	Age started smoking
	Number of cigarettes smoked per day
	Smoking partner
	Intention and motivation to quit
Obstetric characteristics	Use of birth control
	Number of living children
	Number of miscarriages/stillbirths
	Number of premature births
	Number of children born small for gestational age
	Number of children born with congenital abnormalities
	Number of deceased children
Identity	Different statements concerning smoking, alcohol use and motherhood

At inclusion, smoking will be confirmed with a hand-held CO monitor (Micro + smokerlyzer)^52^ and a urinary cotinine test^53^, and alcohol use via a PEth^54,55^ test in 10 mL of blood. The cut-off value to identify active (as distinguished from passive) smoking in our study will be 7 ppm, in accordance with the NICE guideline^56^. Urinary cotinine values above 50 µg/L will be considered indicative of active (distinguished from passive) smoking. Whole blood PEth values above 6 µg/L will be considered indicative of alcohol use in the previous 2 weeks. If participants report smoking cessation during the study period, this will be validated with the CO test. At the primary endpoint, smoking cessation will be validated with the CO test and the urinary cotinine test. Cessation of alcohol will be validated with the PEth test.

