**Table 1 Tab1:** Summary of the lessons of the focus group study that were implemented in the design (detailed results and illustrative quotes are shown in Supplementary Table 4).

Part of SAFER pregnancy intervention	Implementation in the SAFER pregnancy intervention
Home visit and quit plan	Set a quit date, identify potential difficult moments, plan distraction and discuss the habit of smoking and dealing with habits. Discuss how to deal with relatives who smoke and do not smoke. Discuss the option of using nicotine replacement therapy during pregnancy.
Group sessions	Only focus on women who are pregnant or want to become pregnant. Each session is a standalone session so women who already quit smoking share their experiences with women who did not quit smoking yet. Exchange tips and tricks and discuss nicotine replacement therapy. Discuss hazards of smoking and alcohol consumption before and during pregnancy during an interactive and informative session. Focus group sessions on dealing with stress, distraction from smoking, identity, and diet. Let the informative session be guided by an experienced lifestyle coach who knows different ways of cessation.
Online platform	Actively refer participants to an online platform that provides help 24/7.
Incentives	Let women choose which reward they prefer for cessation. Provide monthly incentives instead of one large incentive over a longer period of time. Make the value of the incentives larger over time to motivate quitting early during pregnancy and remaining abstinent over a longer period of time.
Validation	Only provide incentives after biochemical validation.
Costs	Participation should be free.
Other	Give information on cessation support for partners.

Due to the low number of participating women, data saturation might not have been reached. Given the difficulty in recruiting women for the focus groups and in the light of the relevant information collected to inform the design of the SAFER pregnancy study, we pragmatically decided to proceed with finalising the development of the intervention and to start piloting it.

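### Requiring urinary cotinine as well as CO at the primary endpoint can count women who stopped smoking with nicotine replacement therapy as smokers

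*Protocol article*

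**What the plan says.** The outcomes section defines the endpoint in terms of smoking, not nicotine: "The primary outcome is biochemically validated cessation of smoking or alcohol use at" one of three time points, which depend on pregnancy status.

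The data collection section fixes the tests and cut-offs:
- For CO: "The cut-off value to identify active (as distinguished from passive) smoking in our study will be 7 ppm".
- For cotinine: "Urinary cotinine values above 50 µg/L will be considered indicative of active (distinguished from passive) smoking".
- During the study: "If participants report smoking cessation during the study period, this will be validated with the CO test".
- At the end: "At the primary endpoint, smoking cessation will be validated with the CO test and the urinary cotinine test".

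Table 1, in the focus group results, lists what was built into the intervention. Under the home visit and quit plan it has "Discuss the option of using nicotine replacement therapy during pregnancy", and under the group sessions "Exchange tips and tricks and discuss nicotine replacement therapy".

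NRT use is not among the exclusion criteria (setting and participants) or the questionnaire items in Table 4. The article does not say how a woman with CO below 7 ppm and cotinine above 50 µg/L is classified.

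**The concern.** Cotinine is a metabolite of nicotine and does not show where the nicotine came from. The only alternative source that the article considers is passive smoke. In a programme that raises NRT with participants, NRT is a foreseeable second source. A woman who has stopped smoking and is on NRT at the endpoint can be CO-negative and cotinine-positive. If both tests must be negative, she is a smoker for the primary outcome.

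The error runs in one direction: NRT can turn a true quitter into an apparent smoker, but not the reverse. Three results would carry it:
- the quit proportion that is compared with 9% and meant to inform a larger randomised trial;
- the cost per successful quitter, where such a woman's vouchers count as cost while she does not count as a success;
- the backward logistic regression for predictors of effectiveness, which uses the same outcome.

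**Working it through.** **Step 1. Follow one woman through the stated rules.** She smoked at inclusion, has stopped, and still uses NRT at the endpoint.

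| Occasion | Test in the article | Her possible result | Classification |
|---|---|---|---|
| Group session | CO only | below 7 ppm | quit, voucher issued |
| Primary endpoint | CO and urinary cotinine | CO below 7 ppm, cotinine above 50 µg/L | smoker, if both tests must be negative |

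She is not smoking on either occasion.

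**Step 2. Reproduce the planned sample size.** Inputs from the sample size section: null proportion p0 = 0.09, true proportion p1 = 0.25, power 90%, one-sided alpha 2.5%, dropout 25%.

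n = [(z(0.975)·√(p0(1−p0)) + z(0.90)·√(p1(1−p1))) / (p1−p0)]²

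= [(1.960×0.2862 + 1.282×0.4330) / 0.16]² = 48.6, rounded up to 49.

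Dropout: 49 / (1 − 0.25) = 65.3, rounded up to 66. Both figures agree with the article, so the sample size is not in error.

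**Step 3. Effect on the observed rate.** Let s be the share of true quitters who fail cotinine only because of NRT. The article gives no value, so s is an assumption. The observed rate is 0.25 × (1 − s).

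**Step 4. Effect on power at n = 49.** Normal approximation, consistent with Step 2:

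power = Φ{[(p − 0.09)·√49 − 1.960×0.2862] / √(p(1−p))}

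For s = 10%, p = 0.225: (0.135×7 − 0.5609) / 0.4176 = 0.920, and Φ(0.920) = 0.82.

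Exact binomial: the smallest cut-off that keeps the one-sided type I error within 2.5% is 10 or more quitters of 49 (actual error 1.1%). A cut-off of 9 or more has an actual error of 2.9%, above the stated level, so it is not used here.

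| Assumed s | Observed rate | Power, normal | Power, exact (10 or more) | Evaluable women for 90% power (normal) |
|---|---|---|---|---|
| 0 | 25% | 90% | 82% | 49 |
| 10% | 22.5% | 82% | 69% | 66 |
| 20% | 20% | 70% | 53% | 96 |
| 30% | 17.5% | 54% | 35% | 152 |

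**Step 5. The stated denominator.** The data analysis plan takes the number who quit "divided by the total number of women included in the study". If all 66 are analysed and 25% is taken as the true rate among them, normal-approximation power is 96% at s = 0 and 90%, 80% and 63% at s = 10%, 20% and 30%. The loss starts from a higher level, but the fall in the observed rate is the same.

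**The case against.** **The text is softer than it may seem.** A reader might infer that the programme supplies NRT and that every woman who quits with it is scored as a smoker. The article supports neither. It says that NRT is discussed, and it describes the intervention as a web platform, group sessions and incentives. It calls high cotinine indicative of smoking and spells out no rule for discordant results. That both tests must be negative is the natural reading, but an inference. The full protocol may hold a rule that the article omits.

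**Few women may be affected.** Only those still on NRT at the endpoint, with cotinine above 50 µg/L, are at risk. NRT used around the quit date matters only if it continues. Women enrolled for alcohol alone are untouched.

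**The magnitude is hypothetical.** The share s has no source in the article. The 25% was set from another trial's 22.5%, and the article does not say how that trial validated cessation; the planning value may already include such a loss. The study's stated overall aim is an estimate of potential effectiveness, so bias matters more than power.

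**The two-tier testing is deliberate.** A reader might call CO-only validation at sessions a contradiction of CO plus cotinine at the end. It is not: a quick test for vouchers and a stricter final test is an openly stated design.

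**The strict rule errs on the cautious side.** In an uncontrolled study against a fixed 9%, undercounting quitters is the safer error.

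**What stands.** These points limit the wording and the size, but do not remove the problem. The article goes as far as naming tests, cut-offs and timing, and the rule so stated can give a wrong answer for a foreseeable group. Table 3 keeps the result of every biochemical assessment, so rates with and without cotinine could both be reported later. Without a record of NRT use, though, a cotinine-positive quitter on NRT could not be told from a woman who smoked recently but passed CO. Caution is also not the same as accuracy when the estimate is meant to inform the next trial.

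**Conclusion.** The concern holds in a limited form. As written, and on the natural reading that both tests must be negative, the endpoint rule can count women who have stopped smoking but still use NRT as smokers. The validated smoking quit rate is then biased downwards. The size cannot be determined from the article. The falls to 22.5%, 20% or 17.5%, and the matching losses of power, illustrate assumed shares of 10%, 20% and 30%; they also assume that 25% is the quit rate before this misclassification. They are not estimates. The sample size calculation itself is correct. This should be fixed before outcomes are known, but it does not undermine the study as a whole.

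**What to change.** 1. Add one item on current use of nicotine products (NRT, e-cigarettes) at each validation and at the primary endpoint.
2. State in advance that women who report such use are classified as having stopped smoking on CO below 7 ppm plus self-reported abstinence from smoking. In all other women, require the cotinine criterion as well as CO.
3. Report the result with CO and cotinine required for everyone as a sensitivity analysis.

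If the full protocol already has a rule for discordant results, the article needs only a sentence stating it.

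The cost is one questionnaire item and a sentence or two in the endpoint definition; no new test is needed. The drawback is that CO has a shorter detection window than cotinine, so some intermittent smokers who report NRT could count as quitters. Showing both results bounds that error. The change concerns outcome classification only and recommends nothing about the use of NRT.
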